## Abstract

**Background:**

Exercise referral schemes are recommended by the National Institute for Clinical Excellence (NICE) for physical activity promotion among inactive patients with health conditions or risk factors. Whilst there is evidence for the initial effectiveness and cost-effectiveness of such schemes for increasing physical activity, evidence of long-term effects is limited. Techniques such as goal setting, self-monitoring and personalised feedback may support motivation for physical activity. Technologies such as activity monitoring devices provide an opportunity to enhance delivery of motivational techniques. This paper describes the PACERS study protocol, which aims to assess the feasibility and acceptability of implementing an activity monitor within the existing Welsh National Exercise Referral Scheme (NERS) and proposed evaluation methodology for a full-scale randomised controlled trial.

**Methods/design:**

The PACERS study consists of a pilot randomised controlled trial, process evaluation and exploratory economic analyses. Participants will be recruited from the generic pathway of the Welsh NERS and will be randomly assigned to receive the intervention or usual practice. Usual practice is a 16-week structured exercise programme; the intervention consists of an accelerometry-based activity monitor (MyWellnessKey) and an associated web platform (MyWellnessCloud). The primary outcomes are predefined progression criteria assessing the acceptability and feasibility of the intervention and feasibility of the proposed evaluation methodology. Postal questionnaires will be completed at baseline (time 0: T0), 16 weeks after T0 (T1) and 12 months after T0 (T2). Routinely collected data will also be accessed at the same time points. A sub-sample of intervention participants and exercise referral staff will be interviewed following initiation of intervention delivery and at the end of the study.

**Discussion:**

The PACERS study seeks to assess the feasibility of adding a novel motivational component to an existing effective intervention in order to enhance effects on physical activity and support longer-term maintenance. The study will provide insight into the acceptability of activity-monitoring technologies to an exercise referral population and delivery staff. Data from this study will be used to determine whether and how to proceed to a full-scale trial of effectiveness of the intervention, including any necessary refinements to intervention implementation or the proposed evaluation methodology.

**Trial registration:**

ISRCTN85785652

## Background

Physical inactivity is a major cause of preventable illness with large costs to the National Health Service (NHS) [1]. Increasing activity at the population level and among at-risk groups is a public health priority [2, 3]. Physical activity interventions for at-risk groups often involve advice and/or signposting from primary care practitioners [4]. Exercise referral schemes (ERS) are one common model [5], usually involving referral to a community-based structured exercise programme. In Wales, the 16-week National Exercise Referral Scheme (NERS) has been running since 2007. A previous effectiveness study of the scheme [6] showed that, at 12 months, NERS was associated with improvements in physical activity for patients at risk of coronary heart disease, but not for those referred for anxiety and depression, despite an improvement in their mental health [7]. The evaluation also showed the base-case incremental cost-effectiveness ratio was £12,111 per quality-adjusted life year (QALY), falling to £9741 if participants were to contribute £2 per session [7]. Qualitative data highlighted a need for post-intervention motivational support to maintain changes [7, 8]. Whilst there is evidence for effectiveness of ERS in increasing physical activity in the short term [9–11], evidence of long-term effects is limited. The Department of Health’s Quality Assurance Framework for Exercise Referral [12] highlights the need to understand how to support long-term maintenance of changes in physical activity.

On entry to an ERS, patients may be initially motivated by external sources such as GP advice to attend [13, 14]. However, sustained changes in physical activity are consistently associated with more internalised, or autonomous, motivation [15–17]. According to self-determination theory [18], the development of autonomous motivation can be achieved through supporting psychological needs for autonomy (volitional and self-endorsed engagement), competence (personal mastery and effectiveness) and relatedness (meaningful interpersonal connections). Thus, developing ways to support these three needs should help to maintain changes in physical activity. Support for this notion is provided by the randomised controlled trial of the Welsh NERS which found increases in autonomous motivation after scheme exit. This increase explained almost half of the between-group difference in physical activity 6 months later [19]. Integrating processes to further enhance and sustain autonomous motivation during and after involvement in an exercise referral scheme may lead to larger effects and longer-term maintenance of these. Existing evidence points to potential motivational effects of techniques such as goal setting, monitoring and personalised feedback on progress towards goals [20, 21] which may support autonomous motivation by enhancing patients’ sense of mastery and competence and are recommended by NICE as core components of behaviour change interventions [22].

Technologies such as activity monitors provide opportunities to enhance delivery of goal setting and feedback, allowing for more frequent and automatic feedback on progress towards activity goals, tailored updating of goals based on achievement and remote contact with intervention providers [23]. In addition to addressing psychological needs for competence, incorporation of social components may support motivation through promoting relatedness to other service users. Research on such technologies in exercise interventions suggests that use can be quickly integrated in participants’ lives [24] and may increase physical activity levels [25–29]; however, overall, the evidence is equivocal [23]. Furthermore, little is known about the acceptability of these technologies to ERS populations or if the benefits will remain once the initial novelty has ceased. Exercise referral patients are a diverse group with a range of ages and conditions. For example, although the average age of participants in the evaluation of the Welsh NERS was 52 years old, the overall ages ranged from 16 to 88. Thus, familiarity with technology and willingness to use it may differ within the group [30]. In addition, participant diversity in terms of socioeconomic status and geographic location may result in differences in access to high-speed internet connections or the hardware required for engaging with some technologies (e.g. personal computer). Hence, prior to a trial of effectiveness, which may be undermined by difficulties integrating technologies into routine practice or facilitating uptake by patients, piloting is required to investigate these issues.

A preliminary investigation [31] tested a protocol for integrating activity monitoring devices (MyWellnessKey, Technogym) and a linked web platform in one local authority area of the Welsh NERS. The study showed potential for using the MyWellnessKey (MWK) devices in the scheme; however, further work is required to understand the feasibility and acceptability of this on a larger scale with a demographically diverse population. In this paper, we describe the protocol of the PACERS study, a pilot trial to assess the feasibility and acceptability of using the MWK activity monitors to promote maintenance of physical activity within NERS. The aim of the study is to evaluate the feasibility and acceptability of the intervention (the MWK) and its proposed evaluation methodology, in order to optimise design and delivery and evaluate whether a full-scale randomised controlled trial of effectiveness is warranted and feasible.

### Study aim

The primary aim of the study is to assess the feasibility and acceptability of implementing the MWK activity monitors within the Welsh NERS as well as the proposed evaluation methodology in order to optimise design and delivery for conducting a definitive evaluation trial.

### Study objectives

The main objectives for this study are to investigate:the fidelity of delivery of the intervention and trial methodology including compliance with study invitation and randomisation processes;the acceptability of the intervention to participants in terms of its usability and likelihood of future use;whether randomisation is acceptable to 50% or more of participants;the feasibility of recruiting 20% or more new NERS patients and retaining at least 80% of participants at 12-month follow-up (T2);contamination, by exploring whether less than 20% of control participants are exposed to the intervention;the effect of the intervention on the main hypothesised change mechanism (autonomous motivation); andthe feasibility of collecting the primary, secondary and process outcome measures and economic evaluation methods.

## Methods

### Study design

The study design is an individually randomised pilot randomised controlled trial, plus a process evaluation and exploratory economic analyses, of implementing the MWK devices within Welsh NERS standard practice. Data will be collected at three time points: baseline (time 0 (T0)), at the end of the 16-week NERS programme (T1) and 12-months post-baseline (T2). Figure 1 shows the study flow diagram. The study was given favourable ethical opinion for conduct in the NHS on 1 December 2015 by the South East Scotland Research Ethics Committee 02 (REF: 189587).

**Fig. 1 Fig1:**
[figure not shown]
Flow diagram of the PACERS study design

### Setting and participants

The study is being undertaken within the Welsh NERS across leisure centres in eight local authority areas in Wales, UK. The eight study sites were purposively selected to reflect a range of urbanisation and geography. Participants are eligible for the study if they (i) are referred into the NERS generic pathway (see Table 1) and (ii) have the capacity to use the activity monitors (i.e. computer access and an email address).

**Table 1 Tab1:** NERS Generic Pathway Criteria

For referral into the NERS generic pathway, patients must:	
- Be aged 16 years or above;	
- Be sedentary (defined as not moderately active for 3 times per week or deconditioned through age or inactivity);	
- Have at least one of the following:	
○ Raised blood pressure 140/90,	
○ BMI > 28,	
○ Cholesterol > 5.0,	
○ Controlled diabetes or impaired glucose intolerance,	
○ Family history of heart disease or diabetes,	
○ At risk of osteoporosis and/or musculoskeletal pain,	
○ Mild arthritis or poor mobility,	
○ Mild-moderate COPD, asthma, bronchitis, emphysema,	
○ Mild anxiety, depression or stress, multiple sclerosis.	

### Recruitment

Participants will be recruited to the trial using opportunistic invites within the existing scheme structure. NERS exercise professionals will provide information about the study to all new generic pathway clients during their first consultation appointment on the scheme. Exercise professionals will transfer the contact details of clients who are eligible for and interested in joining the study to the research team using a secure electronic form. The research team will send a recruitment pack containing full informed consent materials and the baseline questionnaire to interested clients to be returned by post. Participants who return a signed consent form and completed baseline questionnaire will be entered into randomisation. Participants in the intervention group will be sent information about the process evaluation interviews following randomisation and will be asked to express an interest in taking part in the interviews. From those who express an interest, participants will be selected to provide variation in local authority area, age, sex and reason for referral. Where possible, we will interview the same participants at 4 weeks and 12 months. Where not possible, additional participants matched by demographics (e.g. age and sex) will be recruited for 12-month interviews. All NERS staff involved in the study will be invited to participate in the process evaluation interviews. From those who express an interest, two staff members per local authority area will be selected.

### Randomisation

After completion of baseline measures, study staff will randomly assign participants 1:1 to receive either the intervention (NERS plus MWK) or the control treatment (NERS standard practice) via a computer-generated random allocation sequence created by the South East Wales Trials Unit.

### The intervention

The intervention is an enhanced ERS that includes usual care (NERS standard practice) [6] plus an accelorometry-based activity monitor (MyWellnessKey; MWK). The MWK can be used for self-monitoring of physical activity levels in combination with a linked web platform (MyWellnessCloud) and smartphone application (see Table 2). The MWK has been validated in terms of device accuracy at monitoring physical activity level and intensity [32, 33] and utility at fostering increased physical activity levels (high concurrent validity with ActiGraph accelerometer to detect physical activity in laboratory and free-living environments) [34].

**Table 2 Tab2:** Features of the MWK activity monitor and MyWellnessCloud web platform

• Real-time visual feedback via a screen on the activity monitor	
• Detailed feedback on activity levels via a web platform to indicate progress towards goals, time spent in different activity intensities and calories burned	
• Automatised goal setting via an algorithm which sets goals in a stepwise fashion such that forward progression is mastery-based	
• Facilitation of social support for exercise via the web platform (through involvement in group challenges and remote communication with an exercise professional) and smartphone app (the option to share details about activity completed via social media)	
• Free access to the web platform and smartphone application following discontinuation of use of the MWK via manual input or by linking the account to another monitoring device.	

Intervention participants will be provided with a MWK to use for the remaining 12 weeks of their 16-week NERS programme after receiving it at their 4-week consultation and will be encouraged to use it for 36 weeks after they exit the scheme, up until their 12-month consultation when the device will be returned. In current practice, conducting an 8-month telephone consultation to check clients’ progress with exercise is an optional part of standard care. To encourage participants to maintain engagement in the study, we have asked for the telephone consultation to take place with all intervention participants. Table 3 shows how the intervention will be implemented within the scheme.

**Table 3 Tab3:** Implementation of the intervention components

Time point	Exercise professionals	Intervention participants
At 4 week review appointment	Set up participants with a MWC account, configure initial activity goals on the MWK and demonstrate how to use the device and web platform.	Take the MWK home, sign into their MWC account on their home computer and connect their MWK to read data and charge it.
Over the study period (48 weeks)	Interact with participants to monitor and adjust their goals, send positive comments and set up group challenges through direct messaging via a linked website called Professional Cloud.	Use the device daily and connect the MWK to a computer at least twice per week to upload data to the MWC, receive feedback and charge the device. Manually enter information about activity that the device does not readily measure, i.e. swimming, weight training, cycling.
At 8 months from start	Telephone participants to check on their progress with exercising and remind them of the study and encourage use of the MWK, MWC and associated features.	Participants with a MWK continue to use it daily.
At 12 months from start	Exercise professionals will have a consultation with all participants for usual NERS assessments and to collect the MWK.	Hand the MWK back to the exercise professional.

It is anticipated that the intervention will enhance NERS through two key mechanisms: (1) goal setting and personalised feedback elements of the devices will support a sense of exercise mastery and perceived competence; (2) the web platform will provide a sense of relatedness to others via opportunities to communicate remotely with exercise professionals, other NERS clients and social media contacts. It is anticipated that these mechanisms will improve autonomous motivation for exercise, leading to greater maintenance of increases in physical activity, as depicted in the intervention logic model (see Fig. 2).

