### Control treatment

Control participants will receive usual care which is NERS standard practice: a 16-week structured exercise programme which includes consultations with an exercise professional at the start, 4 weeks, on exiting the scheme (16 weeks) and at 12-month follow-up [6].

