### Primary outcome

The primary outcome will be the feasibility and acceptability of the intervention and its proposed evaluation methodology, to inform a decision on whether a full randomised controlled trial is warranted and feasible. This will be assessed against a set of predefined progression criteria related to recruitment and retention rates, exposure to the intervention in both intervention and control groups and acceptability of the intervention, recruitment and randomisation processes to participants. The criteria were agreed by the Trial Steering Committee (TSC) and follow a traffic light assessment system (red = stop; amber = discuss with TSC whether there is enough evidence that sufficient improvements can be made to proceed to full trial without another feasibility assessment; green = proceed) using quantitative measures supported by qualitative data. The criteria, their measurement and assessment criteria are summarised in Table 4. Qualitative data will provide insights into intervention and evaluation design features which need to be retained, or where metrics fall into the amber zone, modifications which may need to be made to improve feasibility and acceptability.

**Table 4 Tab4:** Summary of progression criteria

Progression criteria (PC)	Measures used	Assessment of whether criteria have been met
PC1. Feasibility to recruit a sufficient proportion of new NERS patients to participate in the trial, with appropriate retention rates to 12-month follow-up.	• The percentage of new NERS patients recruited to the trial, and retained at each subsequent follow-up. • Regression models will be used to identify predictors of loss to follow-up (e.g. demographics or baseline motivation).	• If > 20% of new NERS patients recruited = proceed; if < 5% = full-scale trial unlikely to be feasible. If 5–20% the TSC will consider the feasibility of proceeding to a full-scale trial bearing in mind the data and feedback presented and representativeness of the recruited sample, and possible steps to increase the recruitment rate. • If > 80% retained at 12-months = proceed, if < 60% = full-scale trial unlikely to be feasible. If 60–80% the TSC will consider the feasibility of proceeding based on the available data and possible steps to increase retention.

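### The 8-month call, made to keep participants engaged in the study, is requested for the intervention arm only, while PC1 judges 12-month retention on one figure with no split by arm

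*Protocol article*

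**What the plan says.** All references are to the protocol article.

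- **The intervention (text).** In usual care, "conducting an 8-month telephone consultation to check clients’ progress with exercise is an optional part of standard care". For the trial, with the stated aim of keeping participants engaged in the study, "we have asked for the telephone consultation to take place with all intervention participants".
- **The intervention (Table 3, 8 months).** Exercise professionals are to do three things in the call: "Telephone participants to check on their progress with exercising and remind them of the study and encourage use of the MWK, MWC and associated features".
- **Control treatment.** Usual care is described as including "consultations with an exercise professional at the start, 4 weeks, on exiting the scheme (16 weeks) and at 12-month follow-up". An 8-month contact is not listed, and no matching request is made for controls.
- **Primary outcome (Table 4, PC1).** The measure is "The percentage of new NERS patients recruited to the trial, and retained at each subsequent follow-up". The rule is "If > 80% retained at 12-months = proceed", with below 60% read as a full trial being unlikely to be feasible and 60–80% going to the Trial Steering Committee (TSC). No arm is mentioned. The examples given of predictors of loss to follow-up are demographics and baseline motivation.
- **Study objectives.** The retention target is likewise one proportion of participants.
- **Sample size.** The total is 286, giving ±8.2 percentage points for feasibility proportions and 80% power for an effect size of 0.4 on autonomous motivation at 12 months, with 30% attrition assumed.
- **Data collection.** Questionnaires are mailed, and non-responders get telephone and email reminders, with no restriction to one arm.

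**The concern.** A call whose stated aim is to keep people engaged in the study, and which reminds them of it, is a trial-retention procedure. It is requested for everyone in one arm and left to local practice in the other. Two things follow.

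First, retention at 12 months is one of the two numerical parts of PC1, which feeds the decision on a full trial. If the procedure works, it raises retention in the intervention arm more than in the control arm, and a single overall percentage cannot show that. The TSC could read green when the control arm alone would have called for its discussion.

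Second, autonomous motivation at 12 months is the one between-arm comparison for which the article states power. If the arms lose different fractions of participants, and loss is related to motivation, a comparison of those who respond can be biased. The call also adds a personal contact about exercise, which matters for what a difference is attributed to.

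**Working it through.** **1. Reproducing the plan's own figures.**

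Sample size for a standardised difference of 0.4, two-sided 5% (assumed two-sided), 80% power:

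- Normal approximation: n per arm = 2 × (1.96 + 0.84)² / 0.4² ≈ 98.1, rounded up to 99. Total 198, and 198 / 0.7 = 282.9, i.e. 283.
- t-test version: 99.08 per arm, rounded up to 100. Total 200, and 200 / 0.7 = 285.7, i.e. 286. This matches the article.

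Precision: 1.96 × √(0.25 / 143) = 0.082. The stated ±8.2 points is the half-width for one arm of 143. For all 286 it would be 1.96 × √(0.25 / 286) = 0.058. Reporting retention by arm therefore needs no larger sample than the one already planned.

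**2. What the single PC1 rule lets through.**

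Inputs: 286 participants, 1:1 allocation (143 per arm), green above 80%. Since 0.80 × 286 = 228.8, green needs at least 229 retained. The arm-level rates below are assumptions; the article gives none.

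| Intervention | Control | Overall | PC1 overall | Control alone |
|---|---|---|---|---|
| 86% (123) | 75% (107) | 230/286 = 80.4% | green | amber |
| 90% (129) | 71% (102) | 231/286 = 80.8% | green | amber |
| 100% (143) | 61% (87) | 230/286 = 80.4% | green | amber |

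- Limit: with every intervention participant retained, green needs only 229 − 143 = 86 controls, and 86/143 = 60.1%.
- At the article's own planning figure of 30% attrition, control retention would be about 100/143. Green then needs 129/143 = 90.2% in the intervention arm.
- With equal arms, each 10 points added to intervention retention alone adds 10 / 2 = 5 points to the overall rate.

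**3. Size of a possible retention bias at 12 months.**

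Assume a latent response tendency correlated ρ with the outcome, and a fraction p retained. The mean among those retained is shifted by ρ × φ(z) / p, where z is the normal quantile at 1 − p. The bias is the intervention shift minus the control shift, in standard deviations (SD).

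| Retention, intervention / control | ρ = 0.2 | ρ = 0.4 |
|---|---|---|
| 80% / 70% | −0.029 | −0.059 |
| 86% / 75% | −0.033 | −0.066 |
| 90% / 71% | −0.057 | −0.115 |

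Under these assumptions the shift is about 0.03 to 0.12 SD against the intervention, compared with a target of 0.4. Another missingness pattern could change its size or sign.

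**4. Attribution.**

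If the call by itself moved motivation by an assumed 0.10 or 0.20 SD, that would be 0.10 / 0.4 = 25% or 0.20 / 0.4 = 50% of the target effect. The data as planned could not separate that share from the device and platform.

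**The case against.** The strongest reply is that the call belongs to the intervention. Table 3 lists it under the implementation of the intervention components, part of its content is encouragement to use the device and platform, and contact with exercise professionals over the study period is built into the package. This stands for the exercise and device-use content. A reader might infer that the 12-month contrast is confounded by the call. The documents do not support that for the comparison of the whole package with usual NERS; the limit is on attributing a difference to particular components. The reply does not cover the study reminder, which the article justifies by engagement in the study.

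Other points on that side:

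- **Reminders to non-responders are not tied to an arm.** They act directly on questionnaire return, so they reduce the imbalance, but they do not remove it.
- **Pooling is inferred.** PC1 does not use the word, does not exclude a split by arm, and gives its predictors only as examples. A statistical analysis plan may tabulate retention by arm. The decision rule, however, is stated in the article, and it attaches no arm condition.
- **Some controls may get the optional call.** The contrast is requested for all versus optional, not all versus none.
- **Returning the device at 12 months.** A reader might infer that this further favours intervention follow-up. It bears on the 12-month consultation, which both arms are due to have. Autonomous motivation comes from a mailed questionnaire.
- **The control arm as the harder one to retain.** A reader might assume this. Nothing in the article says so.

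**Conclusion.** The point holds, at moderate severity. A procedure aimed at study retention is applied unequally by arm, and PC1 as written cannot reveal the result. That an overall rate above 80% can coexist with control retention anywhere from just above 60% to 80% follows from the rule and 1:1 allocation. How likely this is cannot be derived from the article: the 90% and 71% example is an assumption, and no document gives the effect of the call on retention. It would therefore be too strong to say that intervention retention is propped up; this is an expected direction, not a documented result.

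For autonomous motivation at 12 months, unequal retention can bias the comparison, by roughly 0.03 to 0.12 SD under the assumed selection model. The result can be read as the package against usual NERS, but not as the effect of the device and platform alone.

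This is not a must-fix. Autonomous motivation is a secondary outcome here, arm-neutral reminders exist, and neither the sample size nor the thresholds need to change.

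**What to change.** 1. Take the study reminder out of the one-arm call. Have the research team send an identical, neutral study reminder by email or post to both arms at 8 months. The exercise and device-use content of the call can stay as part of the package.
2. In PC1, present 12-month retention to the TSC by arm as well as overall, each against the existing 80% and 60% thresholds. State that a green overall rate with an amber or red arm goes to TSC discussion. Letting the lower arm decide outright would be a preference about criteria that the TSC agreed, and it is not needed.
3. Name randomised arm among the predictors in the loss-to-follow-up model.
4. Record the 8-month calls actually received in each arm, report them beside the 12-month motivation result, and describe that result as the package versus usual NERS.

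Cost: one message per participant (286 at full recruitment), one extra table, a record of calls, and a PC1 that is slightly harder to pass. The sample size is unchanged, since the stated ±8.2 points already applies to a single arm.
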